## Abstract

**Introduction::**

Implantation failure is the main factor affecting the success rate of in vitro fertilization (IVF) procedures. Studies have reported that uterine contractions (UCs) at the time of embryo transfer (ET) were inversely related to implantation and pregnancy rate, hence reducing the success of IVF treatment. Various pharmacological agents, with the exception of calcium channel blocker (CCB), have been investigated to reduce UC. In this regard, we are presenting a proposal for a double-blind randomized placebo-controlled trial. The trial aims to determine whether nifedipine, a CCB with potent smooth muscle relaxing activity and an excellent safety profile, can improve the outcome of ET.

**Methods and analyses::**

We will recruit 100 infertile women into one of 2 groups: placebo (n = 50) and nifedipine 20 mg (n = 50). Study participants will be admitted 30 minutes prior to ET and given either tablet after their baseline vital signs have been recorded. They will then undergo ET and be observed for adverse events for another 30 minutes post-ET. The primary outcome will be implantation rate and clinical pregnancy rate. Secondary outcomes include adverse events, miscarriage and pregnancy, and neonatal outcomes. Resulting data will then be analyzed using *t* test, Chi-square test, and multivariate test to compare outcomes between the 2 groups for any statistical significance. This protocol has been designed in accordance with the SPIRIT 2013 Guidelines.

Key PointsSignificant preliminary research has been performed to form the basis for the design of this trial.This is a randomized, placebo-controlled, double-blind trial to assess nifedipine's effect and safety at the time of embryo transfers.This study has the potential to provide a foundation for future large randomized controlled trialsThis trial is a well-designed randomized controlled trial to assess clinically relevant outcomes.Main limitation of this study is that uterine contractions are not measured and existing variability in embryo quality.

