## Introduction

1

Assisted reproduction technology (ART), from ovarian stimulation to the choice of catheters in embryo transfer (ET), has benefitted from major advances and improvements in recent years to continue to circumvent human infertility. However, implantation rate (IR) and clinical pregnancy rate (CPR) in women following ET have remained lower than desired. The IR and CPR are dependent on multiple factors such as techniques and materials involved in the ET process, quality of embryo, and also receptivity of the endometrium.^[1]^ Extensive research has been undertaken to understand and to improve the success of ET following in vitro fertilization (IVF)/intracytoplasmic sperm injection (ICSI) cycles.

One of the major limiting factors affecting the success of ET is thought to be the failure of embryo implantation in the uterus. Embryo implantation failure was estimated to be up to 85%^[2]^ and is governed by complex mechanisms depending on the quality of both the embryo and endometrium.^[3,4]^

Although embryonic aneuploidy is thought to be the major embryonic limiting factor for successful implantation,^[3]^ excessive uterine contractions (UCs) has been proposed as the endometrial limiting factor contributing to the reduced IR in IVF/ICSI cycles.^[3–5]^ As contractile or peristaltic activities of the uterus could move the implanted embryo toward the fallopian tube or cervix/vagina^[6]^ or might even expel it completely out of the uterus.^[3,4]^ This peristaltic mechanism toward the fallopian tube has been suggested to be the cause of higher ectopic pregnancy rate seen in ART.^[6,7]^ A recent published study demonstrated that the uterine peristaltic wave frequency before ET was inversely related to CPR in fresh and frozen–thawed cycles.^[7]^

Various pharmacological agents have been investigated to reduce UC since. These include cyclo-oxygenase inhibitors, β2 adrenoreceptor agonists, antiinflammatories, phosphodiesterase inhibitors, progesterone, and antispasmodics^[8–23]^ demonstrating variable results. Atosiban, an oxytocin/vasopressin receptor antagonist, has shown to be the most promising in improving IR and CPR.^[13]^

If excessive UC indeed reduces IR and CPR in women undergoing IVF/ICSI cycles, then it represents a potential target for pharmacological agents to improve the success of IVF/ICSI cycles.

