## Allocation concealment, blinding, and randomization

16

Randomization will be performed, by a research assistance, via a computer generated sequence in blocks of 10 recruited subjects. The allocation ratio into each arm will be 1:1. The randomization will be stratified for age into 2 groups: less than 35 years old and greater or equal to 35 years old. Neither patients nor caregivers will be aware of the allocation.

All clinical staff will remain blinded to allocation of therapy until the statistical data base is cleaned and locked. Unblinding only be done in case of urgent medical need.

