## Analysis plan

18

Primary analysis will occur by the intention-to-treat principle. Statistical comparisons would be carried out using Chi-square test, Fisher exact test, and Student *t* test with the Statistical Program for Social Science (SPSS, Inc., Version 23.0, Chicago, IL). A 2-sided *P* < .05 was taken as statistically significant. Primary and secondary outcomes between placebo group and treatment group would be analyzed using the above statistical comparisons. The baseline demographics of participants, such as age and number of embryo transferred, would also be analyzed to ensure adequate randomization.

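### Embryo quality is named as a driver of both primary outcomes and as a main limitation, yet the stated primary comparison is unadjusted; one prespecified pre-dose embryo-grade covariate would be a cheap, modest improvement

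*Protocol article*

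**What the plan says.** - **Introduction (section 1):** "The IR and CPR are dependent on multiple factors such as techniques and materials involved in the ET process, quality of embryo" and endometrial receptivity. On implantation failure, the same section says that it "is governed by complex mechanisms depending on the quality of both the embryo and endometrium".
- **Key Points (abstract):** "Main limitation of this study is that uterine contractions are not measured and existing variability in embryo quality".
- **Allocation (section 16):** the sequence is generated "via a computer generated sequence in blocks of 10 recruited subjects", with equal numbers planned per arm. On balancing factors, the section gives age alone: "The randomization will be stratified for age into 2 groups: less than 35 years old and greater or equal to 35 years old". No other stratification factor is named.
- **Analysis plan (section 18):** "Statistical comparisons would be carried out using Chi-square test, Fisher exact test, and Student" *t* test, and the primary and secondary outcomes are assigned to these tests. "The baseline demographics of participants, such as age and number of embryo transferred, would also be analyzed", with the stated purpose of checking the randomization.
- **Abstract, Methods and analyses:** a multivariate test is listed beside the *t* and Chi-square tests, with no covariate or outcome attached. Section 18 does not mention it.
- **Eligibility (sections 12 and 13):** fresh and frozen–thawed transfers are both admitted. The only embryo criterion excludes embryos that have had preimplantation genetic screening. There is no stage or grade criterion.

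**The concern.** The article identifies a prognostic factor for both primary outcomes and presents its variability as a weakness of the study. The comparison it then specifies makes no use of that factor. A grade recorded before dosing cannot be affected by a tablet given 30 minutes before transfer, so it would be a legitimate baseline covariate.

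With 50 women per arm and grade not balanced by design, the arms can differ in embryo grade by chance, and an unadjusted difference carries that imbalance with it. Section 11 wants this study to guide larger trials, and section 23 makes a phase II trial depend on a favourable result. A result that moves with the luck of the embryo mix is less useful for both. The multivariate test in the abstract might have been the remedy, but it is undefined there and absent from the section that sets the analysis.

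**Working it through.** **The plan's own figures.** The article gives 50 + 50 = 100 women, two-sided 0.05, and states that no power calculation was done. It gives no event rate, effect size or grade distribution, so there is no power figure to reproduce. Every rate below is an assumption, shown over a range.

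**1. Chance imbalance.** Let the number of good-grade women in each arm be Binomial(50, π). The SD of the between-arm difference in share is √(2π(1−π)/50).
- π = 0.5: SD 10 points. P(difference ≥ 10 points) = 37%; P(≥ 20 points) = 6%.
- π = 0.3 or 0.7: SD 9 points. The probabilities are 33% and 4%.
- At π = 0.5, P(difference ≥ 8 women, that is 8/50 = 16 points) = 13%.

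**2. Effect on the outcome difference.** Shift = imbalance × gap in pregnancy rate between good and other embryos.
- 10-point imbalance, gaps of 10 to 40 points: shift of 1 to 4 points.
- 16-point imbalance, 25-point gap (45% v 20%): 0.16 × 0.25 = 4 points.
- For scale, the SE of the difference at a 30% rate is √(2 × 0.3 × 0.7/50) = 9.2 points.

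**3. Variance explained.** At π = 0.5 and an overall rate of 32.5%, R² = 0.25 × gap² / (0.325 × 0.675). Equivalent extra women = 100 × R²/(1 − R²).

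| Gap | R² | Equivalent extra women |
|---|---|---|
| 15 points | 2.6% | about 3 |
| 25 points | 7.1% | about 8 |
| 35 points | 14.0% | about 16 |

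At R² = 7.1% the SE falls from about 9.4 to 9.0 points, and the 95% half-width from about 18.4 to 17.7 points.

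**4. Power.** Simulation of 40,000 trials per scenario: π = 0.5, 50 per arm, odds ratio 2.36 within grade, unadjusted Chi-square against a Cochran–Mantel–Haenszel test stratified by grade.

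| Control rate, good / other | Control v nifedipine overall | Unadjusted | Adjusted | Change (points) |
|---|---|---|---|---|
| 40% / 30% | 35% v 55.7% | 57.5% | 55.8% | −1.7 |
| 40% / 20% | 30% v 49.1% | 50.7% | 51.7% | +1.0 |
| 45% / 15% | 30% v 47.6% | 44.6% | 48.6% | +4.0 |
| 50% / 10% | 30% v 45.5% | 36.3% | 43.6% | +7.3 |

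A separate simulation put the gain at about 2 to 8 points for gaps of 20 to 40 points, and the loss at about 1 point for a 10-point gap. The low end is therefore 1 to 2 points and the high end 7 to 8.

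**5. Type I error.** With odds ratio 1, both tests reject in 4.8% to 5.1% of trials.

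**6. Dependence on the embryo mix.** Take the 45% / 15% scenario with odds ratio 2.36, in trials with an imbalance of at least 10 points. The unadjusted test finds in favour of nifedipine in 26% of trials when the imbalance favours placebo and in 64% when it favours nifedipine. The adjusted test does so in about 48% and 49%.

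**The case against.** **An unadjusted test in a randomized trial is valid.** This stands. Randomization removes systematic bias, and the ordinary interval already allows for chance imbalance. A reader might infer that the treatment estimate is biased or the false-positive rate inflated; the documents and the simulation do not support that.

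**The article is a condensed account.** Its baseline list is open-ended, and covariates may sit in a fuller document. This stands in part: one cannot conclude that embryo grade is not recorded, or would never be tabulated. But section 18 does more than stay silent. It assigns the primary outcomes to named unadjusted tests.

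**The abstract promises a multivariate test.** True, and that is where a covariate could enter. It is undefined, however, and missing from section 18, so the two places need aligning in any case.

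**Grade is not embryo quality.** This stands. A reader might infer that adjustment would largely remove the declared limitation, so that it could be deleted. The Introduction names aneuploidy as the major embryonic limiting factor, and nothing in the article says that stage or grade captures it. Declaring the limitation was right. Excluding screened embryos also keeps the sample uniform in that one respect.

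**The gain is small and rests on assumed rates.** Also true. A 4-point shift is under half an SE, age stratification may already balance part of embryo quality, and a weak predictor costs a little power. This limits the point to an optional improvement but does not remove it.

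**Conclusion.** The point holds as a minor one. The article names embryo quality as a determinant of both primary outcomes and as a main limitation, then fixes an unadjusted comparison with age as the only stratification factor.

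The cost is avoidable chance imbalance and some precision, not validity. Adjustment is worth about 1 to 2 points of power if the good/other gap is 20 points, rising to 7 to 8 points at 40. A gap of about 10 points brings no gain or a loss of 1 to 2 points. It does not rescue a sample of 100: at 50 per arm, power is about 18% for 30% v 40% and 53% for 30% v 50%.

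These sizes assume a binary grade with half the women in the good group, the event rates shown, and a grade available before dosing. The documents state none of these.

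**What to change.** 1. Record the laboratory stage or grade of the best embryo selected for transfer, before the tablet is given and by someone unaware of allocation. Availability from the laboratory is assumed and should be confirmed. Write down the cut between good and other so that it covers fresh and frozen–thawed transfers and transfers of more than one embryo.
2. State in section 18 that the prespecified comparison of hCG-positive and clinical pregnancy rates adjusts for this one binary covariate, and is reported as an adjusted risk difference with its 95% interval. A Mantel–Haenszel risk difference over the two grade groups would serve.
3. Replace the multivariate test in the abstract with a reference to this analysis, so that the abstract and section 18 agree.
4. Keep residual embryo quality, aneuploidy for example, among the limitations.

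**Cost:** one extra data field and one covariate, with no change to recruitment, treatment or eligibility. Grading is partly subjective, and power falls slightly if grade turns out to predict weakly.

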## Introduction

1

Assisted reproduction technology (ART), from ovarian stimulation to the choice of catheters in embryo transfer (ET), has benefitted from major advances and improvements in recent years to continue to circumvent human infertility. However, implantation rate (IR) and clinical pregnancy rate (CPR) in women following ET have remained lower than desired. The IR and CPR are dependent on multiple factors such as techniques and materials involved in the ET process, quality of embryo, and also receptivity of the endometrium.^[1]^ Extensive research has been undertaken to understand and to improve the success of ET following in vitro fertilization (IVF)/intracytoplasmic sperm injection (ICSI) cycles.

One of the major limiting factors affecting the success of ET is thought to be the failure of embryo implantation in the uterus. Embryo implantation failure was estimated to be up to 85%^[2]^ and is governed by complex mechanisms depending on the quality of both the embryo and endometrium.^[3,4]^

Although embryonic aneuploidy is thought to be the major embryonic limiting factor for successful implantation,^[3]^ excessive uterine contractions (UCs) has been proposed as the endometrial limiting factor contributing to the reduced IR in IVF/ICSI cycles.^[3–5]^ As contractile or peristaltic activities of the uterus could move the implanted embryo toward the fallopian tube or cervix/vagina^[6]^ or might even expel it completely out of the uterus.^[3,4]^ This peristaltic mechanism toward the fallopian tube has been suggested to be the cause of higher ectopic pregnancy rate seen in ART.^[6,7]^ A recent published study demonstrated that the uterine peristaltic wave frequency before ET was inversely related to CPR in fresh and frozen–thawed cycles.^[7]^

Various pharmacological agents have been investigated to reduce UC since. These include cyclo-oxygenase inhibitors, β2 adrenoreceptor agonists, antiinflammatories, phosphodiesterase inhibitors, progesterone, and antispasmodics^[8–23]^ demonstrating variable results. Atosiban, an oxytocin/vasopressin receptor antagonist, has shown to be the most promising in improving IR and CPR.^[13]^

If excessive UC indeed reduces IR and CPR in women undergoing IVF/ICSI cycles, then it represents a potential target for pharmacological agents to improve the success of IVF/ICSI cycles.

Calcium channel blockers (CCBs) are nonspecific smooth muscle relaxants, predominantly used for the treatment of hypertension in adults. It specifically inhibits the transmembrane calcium influx at the voltage-gated L-type channels.^[24]^ Since these channels are expressed widely throughout body, including the myocardial cells, vasculature smooth muscles, and the myometrium, CCB exhibits multiorgan effects.^[25]^ By inhibiting the slow inward current of the action potential via reducing the intracellular levels of calcium,^[26]^ it decreases the contractility of the smooth muscles and hence causes vasodilation, uterine relaxation, and other effects throughout the body.^[24]^

The most widely used and studied CCB is nifedipine, and there is evidence for safety in pregnancy.^[27–31]^ Nifedipine belongs to a subclass of CCB, namely dihydropyridine, which is selective to vascular over cardiac tissues of about 10:1.^[27]^ Nifedipine, as a CCB, has vasodilatory and potent uterine relaxation properties.^[24]^ It appears that nifedipine is a very safe drug with limited major adverse effects and has demonstrated superiority over other drugs, such as labetolol and β2 adrenoreceptor agonists, in the management of preterm labour or pregnancy induced hypertension consistently.^[24,27–29,32–37]^

As nifedipine is an antihypertensive and has cardiodepressive effect,^[38]^ patients who suffer from hypotensive or compromised cardiovascular conditions are contraindicated to the use of nifedipine.^[34]^ For others, the most common maternal side effects, when nifedipine is used in a therapeutic range, are: transient facial flushing, headache, nausea, tachycardia, and hypotension; less common side effects are: palpitations, dizziness, chest pain, nasal congestion, oedema, and heartburn.^[25,28,37,39–40]^ These side effects are mostly benign and are resolved spontaneously or by withdrawal of administration.^[37,39–40]^ Naturally, adverse events vary according to the total dose of nifedipine^[28]^ and these data arise from studies based on multiple dosing regimen but no data are available for a single dose regimen. Current recommended maximum dosage is 120 mg per day^[31]^ but maximum dose of 160 mg per day has been reported to achieve tocolysis with no increase in maternal side effects in 1 study.^[41]^ Nevertheless, caution should be exercised when prescribing any medication in any clinical scenario.

There is currently no evidence to demonstrate nifedipine toxicity on human embryos.^[42–46]^ More importantly, a long-term study following 94 neonates for up to 18 months of life has found no impact on malformations, diseases incidences, motor function, or childhood education following nifedipine exposure in utero^[47]^ while another large case–control study also found no increased in congenital anomalies risk.^[48]^ Improved neonatal outcomes, such as neonatal morbidity, have also been demonstrated over other tocolytics and antihypertensives in the treatment of pregnancy induced hypertension and preterm labor.^[28,32,36,49,50–56]^

## Rationale

2

Implantation failure remains a major factor affecting the success rate of IVF treatment. There is enough evidence to demonstrate that excessive uterine activities are detrimental to the outcome of ET. Given nifedipine's potent uterine relaxing properties and excellent safety profile, it is a promising candidate to improve IVF outcomes. There is a dearth of information in the literature regarding the use of nifedipine in ART. Therefore, the objective of this study is to evaluate the efficacy of nifedipine administration in improving implantation and pregnancy rates in IVF/ICSI fresh and frozen–thawed ETs.

## AIMS

3

We aim to establish the clinical benefit and other outcomes of ET from a single-dose nifedipine administration as a smooth muscle relaxant.

Specific outcomes are:(1)IR(2)CPR(3)Adverse events rate, including miscarriages(4)Live birth rate(5)Pregnancy and neonatal outcomes

## Methods and analyses

4

This protocol has been designed in accordance with the SPIRIT 2013 Guidelines. Recruitment will start from the end of 2016 for approximately 12 months. Analysis and dissemination will occur after this period of time. Analysis will be by intention to treat and the study is to expect to be completed by the beginning of 2018, approximately the 1st of February 2018, with all live births and secondary outcomes data analyzed.

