## Study setting

7

Patients will be recruited from Melbourne IVF over a period of 12 months. This should allow enough time to achieve adequate participant enrolment to reach target sample size.

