## Secondary outcome

10

(1)Adverse events defined as any unwanted outcomes, such as dizziness or hypotension, reported in this trial.(2)Miscarriage rate defined as loss of a diagnosed clinical pregnancy before 20 weeks gestation.(3)Pregnancy and neonatal outcomes including multiple pregnancy, congenital or chromosomal abnormalities, stillbirth, preeclampsia, delivery before 34 weeks, delivery between 34 and 37 weeks, necrotising enterocolitis, abnormal neurology, placenta praevia, gestational diabetes, low birth weight, admission to neonatal intensive care unit, duration of admission, need and duration of respiratory support, or any other neonatal morbidity reported.

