## Sample size

11

As this is a small scale study, without precedence on which to base accurate power calculations, a power calculation has not been performed. This study should provide guidance for future larger randomized trials. We hypothesis that nifedipine will improve the IR and CPR after IVF/ICSI cycles. A convenient sample of 100 participants, 50 in each arm, was chosen to assess our primary and secondary outcomes.

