## Participant enrolment

15

This trial will begin recruitment at the level of infertility specialist. Once identified as requiring IVF/ICSI, and satisfying inclusion and criteria, the patient will be provided with detailed written information about the trial protocol. Once informed consent is obtained, then the patient will be randomized to one of the study arms and provided with the trial medication 30 minutes prior to their scheduled ET.

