## Trial modification and discontinuation

20

In the absence of adverse events, the medication regimen will not be modified once started. If other protocol changes are deemed necessary by the investigating team, ethical approval will be sought from approving Human Research Ethics Committee. Once approved, protocol amendments will be notified to all investigators, administrators, and trial participants.

Patients are permitted to withdraw from study participation at any time. The trial will cease follow-up once patients have given birth or when clinical pregnancy is not detected from the trial treatment cycle.

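### Completion by about 1 February 2018 with every birth analysed cannot be squared with 12 months of recruitment from the end of 2016 and follow-up to birth

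*Protocol article*

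**What the plan says.** All references are to the protocol article.

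- **Recruitment.** Section 4 (Methods and analyses): "Recruitment will start from the end of 2016 for approximately 12 months". Section 7 (Study setting) repeats the length: "Patients will be recruited from Melbourne IVF over a period of 12 months".
- **Completion.** The same paragraph of section 4 expects the study to be complete at "approximately the 1st of February 2018, with all live births and secondary outcomes data analyzed".
- **Follow-up.** Section 20 (Trial modification and discontinuation): "The trial will cease follow-up once patients have given birth or when clinical pregnancy is not detected from the trial treatment cycle".
- **Transfer relative to randomisation.** Section 15 (Participant enrolment): the "patient will be randomized to one of the study arms and provided with the trial medication 30 minutes prior to their scheduled ET". Transfer therefore never precedes enrolment.
- **Outcomes that need a birth.** Section 3 (AIMS) lists "Live birth rate". Section 10 (Secondary outcome) includes "delivery before 34 weeks, delivery between 34 and 37 weeks", together with neonatal outcomes.

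**The concern.** The stated date falls only about 1 to 4 months after recruitment ends, which is shorter than one pregnancy. Section 4 therefore promises complete birth data at a time when the women transferred last would still be in the first half, or barely at the midpoint, of pregnancy. It also conflicts with section 20, which keeps women under follow-up until they deliver.

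The document does not say which statement prevails. If the date did, live birth, preterm delivery and neonatal outcomes would be cut off administratively. The cut-off would also be selective: among women transferred in the months before it, the only births seen would be early ones.

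**Working it through.** **Inputs from the document.** Recruitment starts at the end of 2016 and lasts about 12 months (sections 4 and 7). Completion is about 1 February 2018 (section 4). Follow-up runs to birth (section 20).

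**Assumptions not in the document.** Accrual is uniform over 365 days. Embryos are day 5, so transfer is at gestational day 14 + 5 = 19 (a day-3 embryo moves dates by 2 days). The end of 2016 is read as 1 October, 1 November, 1 December or 31 December. There is no delay from enrolment to transfer unless stated.

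**Step 1: can the stated date be reproduced?** Transfer to 40 weeks takes 280 − 19 = 261 days. Counting back, 1 February 2018 − 261 days = 16 May 2017, the last transfer that can reach 40 weeks by the stated date. Twelve months of recruitment would have to start by about 16 May 2016. Starting at the end of 2016 instead leaves about 7.5, 6.4, 5.5 or 4.5 months of recruitment for the four starts. No reading gives 1 February 2018.

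**Step 2: last births, and births outstanding on 1 February 2018.** Last transfer = start + 365 days. Last 40-week birth = last transfer + 261 days. Gestation of the last woman at the cut = (1 February 2018 − last transfer + 19)/7 weeks. Share unobserved = 1 − (16 May 2017 − start)/365.

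| Start | Last transfer | Last woman at cut | Last 40-week birth | 40-week births unobserved |
|---|---|---|---|---|
| 1 Oct 2016 | 1 Oct 2017 | 20.3 weeks | 19 Jun 2018 | 1 − 227/365 = 38% |
| 1 Nov 2016 | 1 Nov 2017 | 15.9 weeks | 20 Jul 2018 | 1 − 196/365 = 46% |
| 1 Dec 2016 | 1 Dec 2017 | 11.6 weeks | 19 Aug 2018 | 1 − 166/365 = 55% |
| 31 Dec 2016 | 31 Dec 2017 | 7.3 weeks | 18 Sep 2018 | 1 − 136/365 = 63% |

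**Step 3: sensitivity, same order of starts.** If every birth came at 37 weeks (259 − 19 = 240 days), the share unobserved is 32%, 41%, 49% and 57%. With 30 days from enrolment to transfer, at 40 weeks, it is 46%, 55%, 63% and 71%.

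**Step 4: tilt towards early deliveries.** The cut was simulated with preterm births spread evenly over 28–37 weeks and term births over 37–41 weeks. With an assumed true preterm share of 10%, 35%, 43%, 51% and 60% of all births are unobserved. The preterm share among observed births becomes 11.7%, 11.9%, 12.3% and 12.8%. A true 8% becomes 9.4–10.3%, and 15% becomes 17.5–18.9%.

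**Step 5: direction depends on the denominator.** Per randomised woman, live birth is understated because ongoing pregnancies count as non-births. Preterm delivery per randomised woman is understated too, although it is overstated among observed births. Miscarriage before 20 weeks is overstated if only resolved pregnancies are counted. With all clinical pregnancies as denominator, it is understated for November to end-December starts, because the last women are only about 7 to 16 weeks pregnant at the cut.

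**The case against.** The strongest reply is that nothing fixes a data cut on 1 February 2018. Section 4 gives an approximate, expected date, and in the same sentence requires every birth to be included. Section 20 follows women to birth. Section 16 ties unblinding to a cleaned and locked database, and section 21 opens the final dataset only once data collection is finished; neither names a date. On that reading the forecast slips and nothing is lost. This stands. A reader might infer that half or more of the births will be missing, but the documents support that only if the date is enforced over section 20. Even then, an October start gives 38%.

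A reader might also infer that miscarriage would be overstated, or that the treatment comparison would be biased. The first depends on a denominator that section 10 does not fix. As for the second, the cut falls on both arms alike under 1:1 blocked allocation, so it mainly costs information and distorts absolute rates.

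The primary outcomes are hCG and ultrasound from 6 weeks (section 9). They would be almost complete on the stated date, except for the last transfers under a start at the very end of December.

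One defence does not stand: that all 100 women might be enrolled early. Recruitment would have to end within about 4.5 to 7.5 months, whereas sections 4 and 7 plan 12. Nor can the word approximately cover the shortfall. From 1 February 2018 to the last 40-week birth is 138, 169, 199 or 229 days for the four starts, or about 4.5 to 7.5 months.

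**Conclusion.** The contradiction is firm. Section 4's recruitment window and completion date cannot both hold with every birth analysed, and the date conflicts with follow-up to birth in section 20. This rests only on the length of a pregnancy, not on the accrual pattern or embryo age.

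The consequence is conditional. If data were cut at the stated date, about 46–63% of 40-week births would be unobserved for November to end-December starts, and about 38% for 1 October, under uniform accrual and day-5 transfer. The tilt to early deliveries among observed births is modest: an assumed 10% preterm share becomes about 12–13%. The document gives no expected pregnancy rate, so these shares cannot be turned into numbers of births. If section 20 governs, no births are lost.

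Severity is moderate: a stated date that the design cannot deliver, which bears on the timing of the live birth, preterm and neonatal analyses but hardly touches the primary outcomes.

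**What to change.** Reconcile sections 4 and 20. Restate completion as the last transfer plus about 9 months, plus time to collect neonatal outcomes and analyse. For November to end-December starts that is not before about July to September 2018. The neonatal allowance should be written down: section 20 ends follow-up at birth, while some section 10 outcomes, such as length of neonatal admission, arise after it.

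Lock and analyse live birth, preterm and neonatal outcomes only at that point. Label any earlier report as covering hCG and clinical pregnancy only.

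The cost is a change of wording and birth outcomes reported about 6–8 months later. No extra participants or procedures are needed.
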